#### *Follow-up evaluation* 

A cost analysis is performed in the *follow-up* evaluation which assesses the course of costs in the Better@Home cohort from GR admission up to three months post-GR. In addition to the costs assessed during inpatient and home-based GR, the healthcare-, family & patient costs made during the three months of follow-up are assessed by a face-to-face interview with the patient. These costs include home care, domestic care, hospital care (inpatient and outpatient), general practitioner consultations, mental healthcare utilization, utilization of allied care professionals, use of assistive devices, and informal care utilization.

#### Both studies

 For both the *comparative* and *follow-up* evaluation, costs are calculated by multiplying the volume with the reference price of the unit obtained from the Dutch manual for economic evaluations from 2024 [36, 37]. Discounting is not applied in this study because to the total follow-up time (i.e., from GR admission to completion of GR trajectory) is expected to be shorter than 6 months.

#### Mixed-methods feasibility study

The feasibility study is conducted with a mixed method approach. It assesses the feasibility of the Better@Home program, as perceived by patients in the Better@Home cohort, their primary informal caregivers, and care professionals involved in their GR treatment. Feasibility is operationalized according to the method of Saunders [38], focusing on the following aspects: performance of the program according to plan, including the extent to which all core elements of the program were provided to the target population (fidelity and dose delivered completeness); extent to which the intended target group for the pathway was reached (reach); the extent to which the patients and informal caregivers actively engaged in the program (dose received exposure); barriers and facilitators that may have influenced the implementation of the program (context); and overall opinion of patients, informal caregivers and care professionals with the program (dose received satisfaction).

Data is collected among the patients of the Better@Home cohort using face-to-face structured interviews and among the informal caregivers using self-administered questionnaires. These structured interviews and questionnaires are administered at admission to GR, after completion of the GR trajectory, and after three months of follow-up. Data among the care professionals are gathered using registration forms, which the care professionals administer after providing home-based therapy and during or after weekly multidisciplinary team meetings. In addition, semi-structured group interviews (one group interview per GR facility) are conducted about two months after the inclusion of new patients in the study is closed. The group interviews are conducted with multidisciplinary project group representatives who led the Better@Home implementation in the eight participating GR facilities. Table 3 presents the data collected for the mixed-methods feasibility study.

**Table 3 Tab3:** Data collection mixed-methods feasibility study Better@Home cohort

Process domain/indicators	Operalization	Admission GR	Post GR	Follow-up 3 months	2 months after closing inclusion
**Reach** Extent to which the intended target group for the pathway was reached	The number who refused, dropped out or completed the pathway.	RF	RR	RR	
	Reasons for refusals and dropouts	RF	RR	RR	GI
**Fidelity and dose delivered completeness** Implementation according to plan	Replace part of inpatient GR with home-based GR	FI	RF FI		GI
	Focus on participation goals inpatient and home-based	FI	RF FI		GI
	Use eHealth to support rehabilitation		RF FI		GI
	Promote self-management		RF		GI
	Close collaboration between all care partners	SQ	RF		GI
**Dose received exposure** Extend to which the patient and informal caregivers actively engaged in the programme	Replace part of inpatient GR with home-based GR		RF FI SQ		
	Focus on participation goals inpatient and home-based	FI	FI SQ		
	Use eHealth to support rehabilitation	FI	FI SQ	FI	
	Self-management		FI SQ	FI SQ	
**Dose received satisfaction** What is the opinion of rehabilitants, their relatives, and healthcare professionals about the programme	Replace part of inpatient GR with home-based GR	SQ FI	RF FI		GI
	Focus on participation goals inpatient and home-based		RF FI		GI
	Use eHealth to support rehabilitation		RF FI		GI
	Promote self-management		RF FI		GI
	Close collaboration between all care partners		FI SQ	FI SQ	GI
**Context** What were barriers and facilitators influencing implementation of the programme	Replace part of inpatient GR with home-based GR				GI
	Focus on participation goals inpatient and home-based				GI
	Use eHealth to support rehabilitation		RF		GI
	Promote self-management		RF		GI
	Close collaboration between all care partners				GI

*PF* Patient file, *FI* Face to face interview patient, *RF * registration form care professionals, *RR* Registration Researchers, *SQ *structured questionnaire primary informal caregiver patient, *GI* Group interview care professionals, *GR* Geriatric Rehabilitation

#### Background characteristics

The following background characteristics are collected among the patients in both the Better@Home cohort and historical control group, at admission to the GR facility: age, sex, living arrangement (alone or with others), and diagnosis relevant for rehabilitation (see Table 2 ). Furthermore, in the Better@Home cohort, the following additional background characteristics are collected during the face-to-face interview: educational level and frailty. Frailty is assessed by the Groningen Frailty Indicator (GFI) [39]. The GFI is a 15-item screening instrument to determine the level of frailty. It measures the loss of functions and resources in four domains: physical (mobility functions, multiple health problems, physical fatigue, vision, and hearing), cognitive (cognitive dysfunction), social (emotional isolation), and psychological (depressed mood and feelings of anxiety). All answer categories are dichotomized, and a score of 1 indicates a dependency problem. The range of the GFI score is 0–15. A score of 4 or higher represents moderate-to-severe frailty [40].

In addition, among the informal caregivers of the patients in the Better@Home cohort, the following background characteristics are measured at the patient’s admission using a self-administered questionnaire: age, sex, relationship to the patient, and travel distance to the patient.

Lastly, among the care professionals who filled in the registration forms, we collect discipline, and among the care professionals participating in the group interview we collect age, sex, discipline, and role in the Better@Home program.

### Data analysis

#### Outcome assessment

Statistical analyses will be performed using the statistical software package IBM SPSS Statistics. For both the *comparative evaluation* and the *follow-up evaluation*, descriptive statistics will be used to describe the background characteristics and scores on the outcome measures at admission to the GR facility of patients and informal caregivers (only in the Better@Home cohort). Furthermore, model assumptions (e.g. normality, linearity) will be checked for each model. If a model assumption is violated, appropriate remedies are considered. Missing data on the outcome variables will be addressed by using mixed models, with missing data on the covariates being addressed by using multiple imputation if the percentage of missing values is more than 5%. Both mixed models and multiple imputation yield unbiased and efficient estimates under the missing at random (MAR) assumption. Lastly, the analysis models for both the *comparative* and *follow-up* evaluations adjust for GR facility using dummy coding, which corresponds to a fixed-effects approach. This method fully accounts for between-center variability [41]. Within-center variability is addressed by adjusting for individual-level characteristics in the models, including age, sex, living situation, and diagnosis. Additionally, frequency matching between the Better@Home cohort and historical control group helps to further the balance. However, while confounding at the center level is not an issue thanks to a fixed-effect approach, we cannot be certain that some relevant confounder is omitted at the subject-level.

#### Comparative evaluation

 A linear two-level mixed model (LMM) will be used, which includes independence in daily functioning (BI) as a dependent variable and GR group (Better@Home versus Care as usual), time, time by GR group interaction and facility by GR group interaction as independent variables. Furthermore, facility, age, sex, living situation (alone versus with others), and diagnosis will be covariates. The choice for a LMM is due to the hierarchical nature of the data and the repeated measures design. Each level in the hierarchy is a contextual variable, and each contextual variable has dependency in the data, which means that residuals will be correlated. For this study, the repeated measures (in time) of the BI is a level 1 variable; the subjects (patients) and their characteristics are the level 2 variable, and the facilities are the level 3 variable. In our LMM analysis, the time factor will be used as a continuous variable (due to the differences between patients in their duration of the GR trajectory). Given that the number of independent variables is limited and that the research question focuses on specific variables (i.e., group in the comparative evaluation, time in the follow-up study), the LMM will be built top-down, starting from the most complex model.

#### Follow-up evaluation

 Similar to the comparative evaluation, a LMM will be used. Here, the COPM-p will be the dependant variable with the COPM-s, BI, and EQ-5D-5 L as secondary outcomes. GR group (Better@Home versus Care as usual), time, time by GR group interaction and facility by GR group interaction are the independent variables. Furthermore, facility, age, sex, living situation (alone versus with others), and diagnosis will be the covariates.

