## Methods

### Study design

The Better@Home study is a cohort study accompanied by a mixed-methods feasibility study (Fig. 1). The Better@Home study includes an outcome assessment to assess the program’s outcomes and a cost assessment to assess the costs in relation to the outcomes. Within the cohort study, two evaluations can be distinguished: [1] a *comparative evaluation*, to assess the outcomes and costs from admission to completion of GR in the prospective Better@Home cohort receiving the Better@Home program, compared to a historical control group who received usual care; [2] a *follow-up evaluation*, to assess the course of the outcomes and costs solely within the prospective Better@Home cohort, from admission to three months post-GR. The *mixed-methods study* is to assess the feasibility of the Better@Home program, from admission to three months post-GR. The mixed-methods study incorporates both quantitative and qualitative methods. It evaluates the program’s reach, performance according to plan, active engagement of patients and informal caregivers, barriers and facilitators affecting implementation, and the opinions of patients, informal caregivers, and professionals on the program.

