We selected the COPM-p as the primary outcome for the *follow-up evaluation* as it fits with the Better@Home program, which focuses on participation in daily life. COPM-p scores are not routinely assessed by GR facilities in The Netherlands and could therefore not be used for the *comparative evaluation*, as this data was unavailable for the historical control group. The following four secondary outcomes are measured: independence in daily functioning (BI), patient satisfaction in performing daily activities (COPM-s) [27], and quality of life (EuroQol-5D-5 L) [33], which focuses on ‘health-related quality of life’ outcomes. The EuroQol-5D-5 L includes five dimensions: mobility, self-care, usual activities, pain or discomfort, and anxiety or depression. Each dimension has five levels, ranging from 1 to 5. A lower score indicates a better perceived quality of life. The fourth secondary outcome, the Caregiver Strain Index (CSI), is assessed among the primary informal caregivers of the patients in the Better@Home cohort [34, 35]. The CSI is a 13-item measure that assesses perceived care burden among informal caregivers. The scoring of the CSI ranges from 0 to 13. A higher score indicates a higher level of perceived strain related to care provision.

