A number of limitations of the design of the *prospective cohort study* are present. First, only one outcome measure and a limited number of background characteristics are available in the historical control group, presenting limitations in the ability to control for potential confounding variables and to fully assess the comparability between groups in the comparative evaluation. This may compromise the internal validity of the study’s findings. Second, there is a reasonable risk of selection bias, although measures are taken to reduce this risk and its consequences by the frequency matching procedure. Third, a randomized or experimental design was considered but deemed not feasible for this study. The study aligns with current developments in healthcare, where home-based geriatric rehabilitation is already being implemented, albeit on a limited scale, as part of usual care. Withholding home-based geriatric rehabilitation from patients who would otherwise be eligible for this care was considered unethical, making randomization inappropriate in this context. As a result, we opted for a historical control group design, recognizing that this decision involves methodological trade-offs, including the potential for residual confounding.

A limitation of the *prospective cohort study* is the lack of historical control group data beyond the completion of GR. While it is still possible to provide insight into the course of outcomes and costs within the Better@Home cohort from GR admission to three months after the completion of GR, the *follow-up evaluation* does not offer the possibility of drawing conclusions regarding the long-term outcomes and costs of the Better@Home program. Moreover, it is important to note that, given the observational design of this study, associations observed within the study context do not imply definitive causal relationships. While measures have been taken to minimize bias, including matching procedures and adjusted analyses, the non-randomized nature of the comparative evaluation requires caution in interpreting our findings, particularly in terms of causality.

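### The follow-up model lists group terms that Better@Home-only data cannot estimate, and a single continuous time term, if carried over, cannot separate change during GR from change after it

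*Protocol article*

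**What the plan says.** Under Data analysis, Follow-up evaluation, the article introduces the model with "Similar to the comparative evaluation, a LMM will be used". It names COPM-p as the dependent variable, with COPM-s, BI and EQ-5D-5L as secondary outcomes, and then states that "GR group (Better@Home versus Care as usual), time, time by GR group interaction and facility by GR group interaction are the independent variables". Facility, age, sex, living situation and diagnosis are the covariates.

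Other sections define who is in this evaluation:
- Study design sets its scope as "solely within the prospective Better@Home cohort, from admission to three months post-GR".
- Table 2 has no control entries for COPM-p, COPM-s or EQ-5D-5L at any visit, and no control column at three months. Controls have BI at admission and post-GR only.
- Data collection, Follow-up evaluation, explains that COPM-p could not serve the comparison, "as this data was unavailable for the historical control group".
- The Discussion lists as a limitation "the lack of historical control group data beyond the completion of GR".

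On time, Data analysis, Comparative evaluation, says "In our LMM analysis, the time factor will be used as a continuous variable". The reason given is that patients differ in how long their GR lasts. The same paragraph names time as the variable of interest in the follow-up study. The follow-up paragraph gives no other coding. The general part of Data analysis, Outcome assessment, says that assumptions, linearity among them, will be checked for each model and remedies considered; none is named.

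**The concern.** The listed terms are those of the comparative model, where they belong. In a single-cohort evaluation they have nothing to estimate, so the specification of the primary follow-up analysis contradicts the design it serves. An analyst who follows the text has to decide what was meant. For BI the choice matters more. Controls do have two BI values, so the listed model would run on both groups and bring controls into an evaluation defined without them.

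The second part concerns the effect of interest. COPM is measured at three visits that span two phases: GR itself and the three months after it. If time enters as one straight line, a single rate covers both. A reader who wants the course of COPM-p could not tell gain during GR from what happened later.

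**Working it through.** The plan gives no figure for this analysis that could be reproduced. Its sample-size figures concern the comparative evaluation and do not bear on the point.

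**1. Which terms can be estimated.** Inputs: eight facilities with dummy coding (7 dummies), and Better@Home patients only. With group G = 1 for everyone:
- G equals the intercept column: 1 redundant term.
- time × G equals time: 1 redundant term.
- facility × G equals the facility dummies: 7 redundant terms.

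Total: 1 + 1 + 7 = 9, whatever the number of diagnosis categories.

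For a column count, assume four diagnosis categories (3 dummies); the article does not give the number. As written: intercept 1 + group 1 + time 1 + time × group 1 + facility 7 + facility × group 7 + age, sex and living situation 3 + diagnosis 3 = 24 columns. A numerical check on a simulated Better@Home-only data set (120 patients, three visits) gave rank 15, and 24 − 9 = 15. Without the three group items, the matrix has 15 columns and full rank.

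**2. What one slope does to a two-phase course.** The article gives no COPM means or GR durations, so the profiles below are assumptions. Each calculation takes common visit times and complete data, and fits a least-squares line to the three visit means.

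Gain of 2.5 points by day 60, then level to day 150; points (0, 0), (60, 2.5), (150, 2.5):
- Mean time = 210/3 = 70; mean score = 5/3 = 1.667.
- Sum of squares of time = 70² + 10² + 80² = 11,400.
- Cross-product = (−70)(−1.667) + (−10)(0.833) + (80)(0.833) = 175.
- Slope = 175/11,400 = 0.01535 per day.
- Fitted change during GR = 0.01535 × 60 = +0.92 (assumed truth +2.5).
- Fitted change afterwards = 0.01535 × 90 = +1.38 (assumed truth 0).

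Other assumed profiles:

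| Profile | GR duration | Fitted change during GR (truth) | Fitted change afterwards (truth) |
|---|---|---|---|
| 2.5-point gain, plateau | 45 days, then 90 | 150/9,450 × 45 = 0.71 (2.5) | 150/9,450 × 90 = 1.43 (0) |
| 2.5-point gain, plateau | 90 days, then 90 | 225/16,200 × 90 = 1.25 (2.5) | 1.25 (0) |
| Means 4, 7, 7 | 6 to 12 weeks, then 13 | 0.80 to 1.42 (3.0) | 1.72 to 1.54 (0) |
| Means 4, 7, 6 | 6 to 12 weeks, then 13 | 0.46 to 0.93 (3.0) | about +1.0 (−1.0) |
| Same weekly rate in both phases | 6 to 12 weeks, then 13 | exact | exact |

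The distortion comes from unequal rates. It disappears when the rates are equal, and with partial loss after GR the fitted change has the wrong sign.

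**3. After the change.** Time as a three-level visit factor, or as two slopes, adds one column to the 15, giving 16, and makes the two phase changes separately estimable.

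**The case against.** A reader might infer that the primary model cannot be fitted at all. The documents do not support that. Software that sets redundant parameters to zero returns the reduced Better@Home model, and the time effect, which the article names as its target, is unaffected. This stands: the error is a specification that contradicts the design, not a lost analysis.

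A reader might also infer that the analysis will misstate the course. That needs three steps that the article does not settle:
- The time coding is stated under the comparative evaluation. Its carry-over is a fair reading of the two paragraphs, but still an inference.
- Continuous need not mean one straight line; piecewise or curved time is continuous too.
- The planned linearity check could lead to a remedy.

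All three limit the claim to what can happen. They do not remove it: with no remedy named, the form of the key effect could be chosen after the data are seen.

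It is also tempting to set +0.92 against the 1.3-point minimally important difference. The article defines 1.3 as a difference between measurements, whereas +0.92 is a slope times a duration under an assumed profile. The comparison is too loose to carry weight.

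On BI, the statements that follow-up concerns Better@Home alone make it unlikely that controls are meant to enter. Only the model sentence leaves that open. Finally, visit coding alone would discard the stated reason for continuous time, namely varying GR duration. That objection is sound, and the remedy should allow for it.

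**Conclusion.** The contradiction is established from the text and needs no assumption beyond eight dummy-coded facilities. The follow-up model names three group items, nine terms in all, that are not estimable for COPM-p, COPM-s and EQ-5D-5L. For BI, the sentence leaves room for controls with no three-month value. It should be corrected because it specifies the primary analysis of one of the two cohort evaluations.

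The time part is conditional. If time enters as a single straight line and the rate of change differs between GR and the three months after it, one slope cannot separate the phases and can misstate both. The figures (+0.92 and +1.38 under the 2.5-point plateau) illustrate the mechanism and do not predict this study's result.

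**What to change.** In Data analysis, Follow-up evaluation:
- Delete group, time-by-group and facility-by-group.
- State that the model uses Better@Home patients only, for every outcome including BI.
- Let time differ by phase. One option is a three-level factor (admission, post-GR, three months). The other, which keeps the allowance for varying GR duration, is continuous time with a change of slope at each patient's GR completion. Choose one in advance.
- Report admission to post-GR and post-GR to three months separately. With the two-slope form, state the durations over which the slopes are converted to changes.

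The cost is a change of wording and one extra degree of freedom for time. No new data are needed.

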#### Cost assessment

*Comparative evaluation.* For the cost-effectiveness study, descriptive statistics are used to present mean volumes and costs of healthcare use at baseline. Baseline costs are compared with non-parametric bootstrapping (5,000 times). Statistically significant differences in costs are determined using a 95% Confidence Interval. If the value ‘0’ is included in the confidence interval, this indicates no cost difference between the groups. The incremental cost-effectiveness ratio (ICER) expressed in cost per unit of activities of daily living is estimated as the difference in outcomes on the BI between the Better@Home cohort and historical control group divided by their differences in costs. To characterize sampling uncertainty when estimating the ICER, the costs and effects are also bootstrapped (5,000 times). The resulting 5,000 cost-effectiveness ratios are presented on two incremental-cost effectiveness planes with four quadrants. When performing bootstrap analyses, a higher score represents a positive outcome. Therefore, only for bootstrapping purposes, the BI scores are reversed (a higher score representing less dependence on activities of daily living). Additional sensitivity analyses are conducted to evaluate the robustness of the results. These analyses will at least include a complete case analysis and an analysis of the healthcare perspective instead of the societal perspective. Lastly, given the observational design, the analysis aims to explore whether home-based GR is associated with comparable or improved outcomes at lower or similar costs. If home-based GR results in cost savings with comparable outcomes, a cost-minimization approach will be applied. If both incremental costs and outcomes are positive, the incremental cost-effectiveness ratio (ICER) will be estimated to assess the additional cost per unit of effect.

*Follow-up study.* The course of the costs in the two measurement periods (i.e. the period from GR admission to post-GR, after completion of the GR trajectory; and three months of follow-up post-GR) are analyzed using descriptive statistics.

